### Serious Adverse Event (SAE)

An important medical event, regardless of dose, requiring medical or surgical intervention to prevent serious outcomes (death, life-threatening situation, hospitalization, significant disability or incapacity). This shall be reported by the investigator within 24 hours.

For each SAE, the relationship with the study drug will be assessed and followed up by the principal investigator to allow assessment of reversibility.

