### **Registration of Effect**

The following parameters will be assessed in the children emergency room: Change in dehydration score after placebo/ondansetron followed by ORT, number of vomiting episodes, number of diarrhoea episodes, tolerance of ORT, the volume of ORT, need of i.v. rehydration and needs of hospitalization.

The patient will be phoned 24-72 hours after returning home, by a person from the research team, and asked about information about the general condition, number of diarrhoea and vomiting episodes and possible side effects of the drug.

Stool samples will be collected from the participants of the study. The sample is taken with a small spoon (about 5 ml volume). From small children sample taken from the diaper. If it's just fluid in the diaper this can be pushed out with a spoon. Stool samples will be routinely analyzed at the microbiological laboratory at Sahlgrenska Hospital and then sent to the Department of Molecular Virology at Linköping where characterization of rotavirus and norovirus will be performed [19, 20].

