### Undesirable event - 'Adverse Event (AE) "

Adverse events are all adverse events occurring during the study, regardless of whether they are related to the study drug or not. All these are assessed by the principal investigator and recorded in the investigator's brochure. Concurrent illnesses reported at baseline will not be reported as "undesirable events" (AEs). However, a worsening of the patient's disease during the study should be assessed as an AE SAE options depending on what happened. The patient can always visit the emergency room for AEs, and the emergency room is open all hours and all staff are familiar with the study. Principal investigator (or other investigators delegated by the principal investigator) will be available 24 hours a day on the phone.

The severity is judged by the following:

Mild AE = AE tolerated easily:

Side effects of the drug such as headache, feeling hot, dizziness, fatigue, hiccups, and coughs. Adverse events in previous studies show that 90% had a feeling of fatigue and a few got a cough (27).

Moderate AE = AE which affect the ability of the patient to normal activity and provides significant discomfort:

Mild to moderate dehydration, transient. Constipation.

Severe AE = an AE which largely affects the ability of the patient to normal activity and causing great discomfort.

For serious AE, the relationship with the study drug should be assessed ( 'not related', 'possibly related' or 'probably related'). AEs judged to be related to study drug will be followed up by the principal investigator to allow assessment of reversibility.

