### SUSAR reporting ( "Suspected Unexpected Serious Adverse Reaction"

Side effects that occur and which are not included in the SPC in FASS will be reported by lead investigator as follows:

A suspected unexpected serious response reaction to the study drug (SUSARs) that are fatal or life-threatening should be reported to the Medical Products Agency (MPA) and the Local Ethical Committee (REPN) within 7 days of date from that the principal investigator became aware of the incident. Completion of the report should be sent to the authorities within a maximum of 15 days.

A suspected unexpected serious response reaction to the study drug (SUSARs) that are not fatal or life-threatening should be reported to LMV and REPN within 15 days from the date that the principal investigator became aware of the incident. Completion of the report should be sent to the authorities as soon as possible.

When SUSARs occurring in Sweden in an investigator-initiated study of non-commercial sponsor, who is not able to directly report to the European database on adverse effects (the so-called testing module of EudraVigilance), a CIOMS form (available at the NLS website) can be used. This form is sent to [[contact]](mailto:[contact]).

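### The SAE definition, read literally, leaves out events that are themselves fatal, life-threatening or lead to admission; the follow-up question and the place of AE recording also need correcting

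*Protocol*

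**What the plan says.** Protocol, Serious Adverse Event (SAE), gives one definition: an important medical event, whatever the dose, "requiring medical or surgical intervention to prevent serious outcomes (death, life-threatening situation, hospitalization", or significant disability or incapacity). The reporting duty follows directly: "This shall be reported by the investigator within 24 hours". No other section adds a further category of SAE.

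The SUSAR reporting section sets a 7-day limit for suspected unexpected serious reactions "that are fatal or life-threatening should be reported to the Medical Products Agency (MPA") and the ethics board, and 15 days for those that are neither fatal nor life-threatening.

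The Adverse Event (AE) section is broad on cause: "Adverse events are all adverse events occurring during the study, regardless of whether they are related to the study drug or not". It then fixes where they are kept: "All these are assessed by the principal investigator and recorded in the" investigator's brochure. It adds that a worsening of the child's disease is to be judged as an AE or an SAE according to what happened.

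Once a child has gone home, the scheduled contact is one telephone call after 24 to 72 hours. Registration of Effect lists its content as general condition, "number of diarrhoea and vomiting episodes and possible side effects of the drug". Study Design gives the same content as an open list of examples.

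**The concern.** An SAE definition normally starts from outcomes: the event was fatal, was life-threatening, led to admission, or left disability. The clause on important medical events that need intervention is an addition for events that were headed off. Here the addition is the whole definition, and the outcomes appear only in brackets as things to be prevented.

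At stake is the trigger for expedited reporting in a placebo-controlled trial that enrols children from 6 months of age for a new indication. Admission is no remote possibility, because need for hospitalisation is one of the recorded parameters and admitted children stay in the study. Investigators will have to decide whether an admission is an SAE, and the text does not let them decide consistently.

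The other two points bear on how complete the AE record is. A guardian asked about side effects of the drug must first guess whether a symptom came from the drug or from the illness. The named place of recording is also not a per-patient document.

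**Working it through.** No arithmetic applies: the protocol gives no SAE or AE figure of its own for the trial. The check sets the sections side by side.

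**1. SAE definition applied to cases**

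| Case | Literal reading of the SAE section | Other text |
|---|---|---|
| Child dies with no intervention attempted | Not met: nothing was required to prevent the outcome | If a suspected unexpected reaction, the SUSAR section sets 7 days |
| Hypersensitivity reaction treated to avert death | Met | – |
| Intravenous fluid given so that admission is avoided | Can be met | Need for i.v. rehydration is also a recorded parameter |
| Child admitted as gastroenteritis worsens | Unclear: admission has occurred, so it was not prevented; met only if treatment is seen as averting something worse | AE section: judge as AE or SAE; need for hospitalisation is also a recorded parameter |

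The first case falls outside the definition. The third may fall inside it although the outcome is milder than in the fourth, which is unclear. The definition can therefore under-capture and over-capture.

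**2. Fit with the SUSAR section.** A SUSAR must be serious to count as one. A rule for fatal or life-threatening SUSARs presupposes that being fatal or life-threatening makes a reaction serious. The SAE section does not say so.

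**3. Whether the AE section repairs it.** It sends worsening disease to an AE-or-SAE judgement but gives no criterion of its own. The judgement goes back to the SAE definition.

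**4. AE definition against the call.** The definition counts events "regardless of whether they are related to the study drug or not". Of the four listed topics, two are vomiting and diarrhoea counts, one is general condition, and one is side effects of the drug. The last is the only one that asks about adverse events as such, and it is tied to the drug. The protocol itself names fatigue, headache and constipation as possible drug effects. Guardians could plausibly put fatigue or headache down to the infection and not mention it.

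**5. Place of recording.** The Attachments list glosses the investigator's brochure as a user's handbook. Quality Control and Quality Assurance has the monitor check that correct study data are collected in the CRF, and the section on other drugs sends analgesic use to the CRF. As written, AEs alone go to a document that is not the per-patient record.

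**The case against.** The strongest reply is that the practical gap is small, and much of that reply stands.

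- **Every admission escapes the rules.** A reader might infer this, but the documents do not support it. Need for hospitalisation is a recorded study parameter, worsening must be assessed as AE or SAE, and some treated admissions would meet the SAE text. Admissions are therefore not lost from the comparison of the arms. What is open is whether they start the 24-hour report.
- **The call asks only about drug side effects.** This is also too strong. The call covers general condition and symptom counts, and Study Design's list is open. Guardians are told to return if the child worsens or passes no urine for 8 hours, an investigator can be reached by telephone at all hours, vital signs are registered during the stay, and findings by a non-study doctor on a return visit go to the principal investigator. These routes limit the risk. After discharge, however, all but the call depend on the guardian acting.
- **Guardians' guesses decide what counts.** The principal investigator assesses all AEs, so guardians do not make the final judgement. The framing can only affect what reaches the investigator.
- **AEs are lost because they go into the brochure.** The wrong place of recording does not by itself lose an event. The wording may be a translation slip, though the text cannot settle that, and the monitor is also to check AE reporting against a named regulation.

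The SUSAR section and the monitor's check show that broader reporting was probably intended. They do not change the SAE definition, to which the 24-hour duty is tied.

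**Conclusion.** The point holds in three parts of unequal weight.

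- **Main:** the SAE definition is wrong as written. It does not cover, as such, events that are fatal, are life-threatening, lead to admission or leave disability, and it does not fit the SUSAR section. It also leaves the status of admission for gastroenteritis unclear.
- **Secondary:** the call's one adverse-event question is narrower than the AE definition and may miss events.
- **Minor:** the investigator's brochure is the wrong place to record AEs.

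The number of events affected cannot be derived from the protocol. The conclusion rests on a literal reading; investigators who apply the usual outcome-based meaning would report more than the text demands. The primary endpoint and the efficacy comparison are not touched. The change should be made because it concerns a safety reporting duty and costs little. The SAE definition, the AE question and the place of recording are fixed in the protocol, so this does not depend on what an SAP may contain.

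**What to change.** 1. Define an SAE as an AE that results in death, is life-threatening, requires or prolongs hospitalisation, or causes significant disability or incapacity. Keep the present important-medical-event clause as an added category.
2. State how admission for the underlying gastroenteritis, which is a planned outcome, is classified and reported. Without this, the new definition would make every such admission an SAE by default and the present ambiguity would not have been settled deliberately.
3. Add one open, cause-neutral question to the follow-up call, asked for every child, about any new or worsened health problem. The investigator then judges causality.
4. Name the CRF as the place where AEs are recorded.

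The cost is amendment wording, one line in the call script and one CRF page. No treatment, visit or sample size changes.

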### SUSAR reporting ( "Suspected Unexpected Serious Adverse Reaction"

Side effects that occur and which are not included in the SPC in FASS will be reported by lead investigator as follows:

A suspected unexpected serious response reaction to the study drug (SUSARs) that are fatal or life-threatening should be reported to the Medical Products Agency (MPA) and the Local Ethical Committee (REPN) within 7 days of date from that the principal investigator became aware of the incident. Completion of the report should be sent to the authorities within a maximum of 15 days.

A suspected unexpected serious response reaction to the study drug (SUSARs) that are not fatal or life-threatening should be reported to LMV and REPN within 15 days from the date that the principal investigator became aware of the incident. Completion of the report should be sent to the authorities as soon as possible.

When SUSARs occurring in Sweden in an investigator-initiated study of non-commercial sponsor, who is not able to directly report to the European database on adverse effects (the so-called testing module of EudraVigilance), a CIOMS form (available at the NLS website) can be used. This form is sent to [[contact]](mailto:[contact]).

## **Statistics**

We will at the time when the children receiving placebo/Ondansetron not be aware of the etiology of children's gastroenteritis. However, the study will be carried out during the high season for viral gastroenteritis. 215 children is the number that will be included and we believe we have sufficient number of children to be able to do statistical calculations. We have no similar studies to relate to, but with previously published data, we estimate that more than 60% of the acute gastroenteritis will be caused by rotavirus (Uhnöo and Svensson, Journal of Clinical Microbiology, Mar. 1986, p. 551- 555; Uhnöo et al, J Infect. 1986 Christmas; 13 (1): 73-89.) and norovirus (CDC), and we believe therefore that 129 children (60%) are sufficient numbers to see a statistical difference. In fact, this study is one of the largest (along with Freedman et al, N Engl J Med 2006; 354: 1698-1705 April 20, 2006, which included 215 children) of the studies whatsoever made by Ondansetron and gastroenteritis on children.

## **Quality Control and Quality Assurance**

Before any study related action/investigation can begin, the patient and their guardians are informed and signed the consent, which should also include that be a monitor and any inspection will have access to patient records, to verify the source data. The head of the department must give their permission for the monitor to have access to relevant patient data in patient records. A confidentiality agreement should be maintained between the head of the department, who is responsible for patient records and the monitor.

Monitoring of the study will be conducted by an independent monitor from Linköping Academic Research Center (LARC).

The monitor will ensure that:

- Compliance with the Protocol
- Correct data will be collected for the study, in "Case Report Form" -CRF
- The adverse events are reported as LVFS 2011: 19
- Handling of the drug is made under the Protocol and regulations for clinical trials.
- Original data and study related documents are available and assessable and that all documentation is saved/archived.

Principal investigator shall ensure that the monitor has access to CRF, patient and original laboratory data, to check the source data relevant to the study, without compromising patient privacy. Principal investigator is also aware that the inspection of the authority might be implemented.

### **Procedure for Recruitment and Obtaining Informed Consent**

Consent process will be carried out in accordance with ICH GCP guidelines and the Helsinki declaration. The guardian (as these subjects are under 18 years) must provide written consent alternative oral consent on the phone (and in retrospect one signature per guardian) to participate in the study, before any study related action can be performed. A copy of the patient information and of the signed consent will be given to the guardian.

A physician will give both oral and written information to the child and its guardians, regarding what a participation in the study means. Guardian and the child will have the opportunity to ask questions. They are also informed that participation is entirely voluntary and that they could at any time decide to terminate the study without medical care deteriorates.

The guardian's signature gives consent to participate in the study, agree monitoring and pharmaceutical authorities to get full access to medical records, etc. (the privacy). Inclusion of patients in the study will start once the written approval of the Regional Ethical Review Board (REPN) as well as authorization from the Medical Products Agency (MPA) is available.

### **Operation and archiving of data**

Patients is identified with his initials and a serial number. The patients' full identity linked to the serial number of the study will be made on a patient identifier list stored in a locked cabinet.

Patient data will be processed and handled by the principal investigator at the Queen Silvia Children's Hospital, Gothenburg.

Principal investigator has a binder with relevant content for the study as patient forms, patient identification list, the original patient information and obtained consent for the study. This binder will be kept away from unauthorized, but the responsible for the study will have full access.

Study document and source data will be archived for at least 10 years after the study report has been written and submitted to the MPA.

### **Insurance**

Patients are insured by the Pharmaceutical Insurance and Patient Injury Act.

### **Reporting and Publishing**

Study data are owned by the sponsor.

Processing of the results will be made as soon as the study is completed, when 215 children have been enrolled in the study. Results from the study will be published in international journals.

## **Attachments**

- Flowchart
- Labeling Proposal and pharmaceutical documentation of placebo and Zofran
- Consent Form
- User's handbook (Investigator's Brochure)
- Written patient information
- CV for researchers with primary responsibility
